**Allocated to intervention**

11 clusters

Average number of ASHAs per cluster:

Average population size:

Range:

Enrolled for baseline survey: n1

**Allocated to intervention**

11 clusters

Average number of ASHAs per cluster:

Average population size:

Range:

Enrolled for baseline survey: n1

Enrolled for baseline survey: n2

**Follow up**

Clusters:

Lost to follow up (n= )

Discontinued intervention (n= )

ASHAs:

Lost to follow up (n= )

Discontinued intervention (n= )

Newly recruited

New pregnancy registrations: (n= )

Live births: (n= )

**Follow up**

Clusters:

Lost to follow up (n= )

Discontinued intervention (n= )

ASHAs:

Lost to follow up (n= )

Discontinued intervention (n= )

Newly recruited

New pregnancy registrations: (n= )

Live births: (n= )

**Analysis**

Clusters:

N clusters (number of clusters excluded)

Discontinued intervention (n= )

ASHAs:

N ASHAs (number of clusters excluded)

Enrolled for endline survey: n2

**Analysis**

Clusters:

N clusters (number of clusters excluded)

Discontinued intervention (n= )

ASHAs:

N ASHAs (number of clusters excluded)

Enrolled for endline survey: n2

**Figure 1 Enrolment and outcomes**

## 6.2 Rationale for design

Randomization is required to minimize risk of bias and to attribute effect to the intervention. Considering complex community based intervention, cluster randomization is required. The ImTeCHO web interface will be primarily used by the PHC staff, including medical officer, and other support staff; thus, unit of randomization will be a PHC to reduce contamination between clusters. A PHC is operational and administrative unit for providing curative and public health services for all villages covered by it. Each PHC has a team of two medical officers and 4 to 6 ANM along with one Lady Health Visitor (LHV) and male multi-purpose workers. Out of two medical officers, one has MBBS degree and is in-charge of PHC, including clinical services. Other medical officer is usually an AYUSH (Ayurveda, Yoga & Naturopathy, Unani, Siddha and Homoeopathy) and is involved in field based duties. Each ANM is in-charge of one sub center which serves population of 3,000 to 4,000. On an average, there are 20-25 ASHAs per PHC. There is one ASHA Facilitator for approximately every 10 ASHAs. Average size of population per PHC is approximately 20,000 in tribal areas[[41]](#footnote-42).

## 6.3 Inclusion and exclusion criteria

All clusters (PHCs) belonging to Valia, Netrang (except those where ImTeCHO is being implemented already as part of another project), Dediyapada, Nandod, Garudeshwar and Tilakwada blocks with 100% rural population and scheduled tribe population of more than or equal to 45% will be eligible to be included. Those PHCs will be excluded where all medical officer posts, and 20% post for ASHAs are vacant at the time of initiation of study. Those PHCs will be excluded whose more than 10% villages have no mobile signal most of the time. Although ImTeCHO mobile application can function without GPRS signal, lack of such signal in large areas of intervention will affect components of intervention to significant extent. PHCs where internet cannot be accessed reliably by medical officer and PHC staff to view web interface and an alternative arrangement is not possible will be excluded too as web interface is important part of the ImTeCHO intervention.

# 7. Study setting

This study will be conducted by SEWA Rural, which is a voluntary organization located in Jhagadia block of Gujarat. SEWA Rural is a voluntary development organization involved in health and development activities in rural, tribal area of Gujarat, India since 1980. From April 2003 to March 2011, SEWA Rural implemented a family centred safe motherhood and newborn survival project covering 171,000 population of Jhagadia block. This project included comprehensive community level interventions which were complemented by First Referral Unit (FRU) providing Comprehensive Emergency Obstetric and Newborn Care (CEmONC) services. Supported by the John D. & Catherine T. MacArthur Foundation, the main goal of this project was reduction of maternal and neonatal mortality and morbidity. There was 75% reduction in maternal mortality and 38% reduction in newborn mortality over project periodError: Reference source not found. A new, unexplored area in Gujarat will be required for conducting this research. We have identified four blocks as potential study area (intervention and control area); all being predominantly tribal. Area profile of all four blocks is described in Table 8. There are total 26 PHCs in these four blocks.

**Table 8: Area profile of Valia, Sagabara, Nandod and Dediyapada blocks (Census 201**1)

|  | Valia | Dediyapada | Nandod | Tilakwada | Netrang | Nandod | Garudeshwar |
| --- | --- | --- | --- | --- | --- | --- | --- |
| Number of Households | 31,591 | 35,271 | 50,839 | 13,240 | Newly created after census 2011 | 50,839 | Newly created after census 2011 |
| Average Household Size(per Household) | 5 | 5 | 5 | 5 | 5 |
| Population-Total | 145,400 | 174,449 | 241,053 | 63,871 |  | 241,053 |  |
| Population(0-6Years) | 17,281 | 27,670 | 27,919 | 7,927 |  | 27,919 |  |
| Sex Ratio | 962 | 977 | 935 | 924 |  | 935 |  |
| Sex Ratio(0-6 Year) | 961 | 961 | 923 | 891 |  | 922 |  |
| SC Population | 1,038 | 498 | 5,645 | 1,965 |  | 5,645 |  |
| ST Population | 113,771 | 168,181 | 176,658 | 35,396 |  | 176,658 |  |
| Sex Ratio (SC) | 1,031 | 844 | 976 | 919 |  | 976 |  |
| Sex Ratio (ST) | 967 | 979 | 940 | 922 |  | 940 |  |
| Proportion of SC (%) | 1 | 0 | 2 | 3 |  | 2 |  |
| Proportion of ST (%) | 78 | 96 | 73 | 55 |  | 73 |  |
| Literates | 93,707 | 94,725 | 166,198 | 44,215 |  | 166,198 |  |
| Illiterates | 51,693 | 79,724 | 74,855 | 19,656 |  | 74,855 |  |
| Literacy Rate (%) | 64 | 54 | 69 | 69 |  | 69 |  |

Valia block belongs to Bharuch district whereas Dediyapada, Nandod and Sagbara blocks are in Narmada district. The four blocks belong to eastern, tribal belt of Gujarat; this tribal belt stretches along the Satapuda mountain range which begins from Dahod in north to Dharampur in south. Most of the Dediyapada and Sagabara areas are covered by thick forest. Ahmadabad is the nearest city with an international airport which is located approximately 250 km from study area. Sagabara, Nandod and Dediyapada borders Maharashtra state on eastern side. Valia’s western part, due its proximity to mega-industrial area of Ankleshwar is rapidly getting urbanized whereas Dediyapada, Sagabara and most of the Nandod have remained rural and remote. The four block capitals are well connected by road to national highways though there are no existing railway facilities in any of the 4 blocks though block capital of Nandod will soon be connected via railways. Block headquarters-Valia, Nandod, Dediyapda and Sagabara are approximately 40 km, 60 km, 60 km and 80 km from SEWA Rural head-quarter which is located in Jhagadia town.

The tribal population residing in the study area is called “Vasava”. As with other tribal communities, Vasava tribe has its own language and customs which are different from mainstream culture though this is changing rapidly as they are increasingly connected with mainstream culture. Agriculture is the main occupation with large number of population working as landless laborers. The rate of industrialization is much slower in case of Dediyapada, Nandod and Sagabara compared to other parts of Gujarat. Dediyapada, Nandod and Sagabara belong to Narmada district which is named one of the *most backward districts* by the Ministry of Panchayati Raj in 2006 considering the lack of development and difficult terrain[[42]](#footnote-43).

# 8. Sample size calculation

Please see Table 9 for sample size calculation and associated assumptions. Based on assumptions listed in the Table 9, eleven clusters (PHCs) will be randomized in each arm with which we will be able to answer the above mentioned questions. The assumptions used for sample size calculation are based on data collected by SEWA Rural in a sample of study area and current area of pilot implementation along with other relevant wide scale surveys by the government. However, there is no existing data available from the whole study area about primary outcome of interest. Hence, sample size will need to be revised based on findings of baseline survey and definition of “success” if large discrepancy is found between current assumptions and baseline survey findings. Considering required sample size of 11 PHCs each in intervention and control area, six blocks (total 26 PHCs, out of which 23 meet all eligibility criteria) listed above should suffice to select study clusters.

As intervention is primarily affecting ASHAs, analysis will be done at ASHA level. Therefore, number of ASHAs per PHC will be used as “cluster size”. Based on indirect information before baseline, we assumed there will be 25 ASHAs in a PHC and MACCI of 36%. In absence of existing information regarding the intraclass correlation (ICC), we will assume ICC to be 0.02. Assuming loss of one cluster per arm and three ASHAs per PHC, for detecting 15% absolute improvement in MACCI in intervention arm compared to control arm at endline survey with 80% power and 5% two-sided significance level, we estimated that required sample size per arm will be 11 PHCs/clusters. Similarly, we assumed 46% of neonates/mothers would receive at least two postnatal home visits within first week of delivery by ASHA in control arm. Assuming loss of one cluster per arm and three ASHAs per PHC, we estimated that required sample size per arm will be six PHCs/clusters for detecting 20% absolute improvement in proportion of neonates/mothers who received at least two postnatal home visits within first week of delivery by ASHA in intervention arm compared to control arm at endline survey with 80% power and 5% two-sided significance level..

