# 6. Study design

## 6.1 Design

This will be a two arm, parallel, stratified cluster randomized trial in which unit of randomization will be a PHC. Stratification is required to ensure that prevalence of primary outcomes are similar in the intervention and control groups along with almost equal selection of PHCs from from the most backward Dediyapada block. Stratification will be also done to improve power and precision. The randomization will be done after baseline survey. Along with primary outcomes, randomization would help to balance cluster size across both groups. The allocation ratio will be 1:1. Stratified randomization will be done by a statistician at AIIMS not involved in implementation of intervention. The baseline variable to be used for stratification will be the primary outcome indicator MACCI. The PHCs in each of the two strata will be randomly allocated into to intervention and control group. The randomization will be done using software nQuery. Due to the nature of the community-based intervention, blinding will not be possible.

Assessed for inclusion: 26 clusters

Randomized: 22 clusters

Did not meet inclusion criteria: 4 clusters

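### Section 8 relies on a post-baseline sample size revision, but the planned frame cannot supply more than the 11 PHCs per arm already used, and 11 leaves no margin

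*Protocol*

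**What the plan says.** Section 8 states that no data on the primary outcome exist for the whole study area. On clustering it says: "In absence of existing information regarding the intraclass correlation (ICC), we will assume ICC to be 0.02". Its safeguard is that the "sample size will need to be revised based on findings of baseline survey", a step that the sentence also ties to how success is defined. The trigger is worded "if large discrepancy is found between current assumptions and baseline survey findings". No threshold is given for a large discrepancy.

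The same paragraph describes the available clusters: "six blocks (total 26 PHCs, out of which 23 meet all eligibility criteria) listed above should suffice to select study clusters". The enrolment flow in Section 6.1 (Figure 1) shows 26 clusters assessed, "Did not meet inclusion criteria: 4 clusters" and "Randomized: 22 clusters". Section 6.1 sets 1:1 allocation and places randomisation after the baseline survey. Section 6.3 limits eligibility to six named blocks and provides no reserve.

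Section 8 takes the number of ASHAs in a PHC as the cluster size: 25, reduced to 22 by an assumed loss of three. It says that 11 PHCs per arm give 80% power (two-sided 5%) for MACCI of 36% versus 51%, with loss of one cluster per arm allowed for. The postnatal-visit outcome (46% versus 66%) is said to need six per arm.

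**The concern.** The revision clause is what stands between an assumed ICC and an underpowered trial. It protects power only if the sample can grow, and Sections 6.1, 6.3 and 8 together leave no room for that. More PHCs are not available within the frame at 1:1, and more ASHAs per PHC are not available because all are counted. A downward revision remains possible but does nothing for power.

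If the baseline survey shows more clustering than assumed, the plan calls for PHCs that it does not have and does not say what happens next. The wording also leaves open whether the definition of success feeds into the revision or may itself be revised. The exposed outcome is MACCI, which alone determines the figure of 11.

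**Working it through.** **Clusters available.**
- Section 8: 23 eligible − 22 randomised = 1 spare.
- Section 6.1: 26 − 4 − 22 = 0 spare.
- One more PHC in each arm needs 24. Under either count the maximum at 1:1 is 11 per arm.

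**Inputs (Section 8 and Table 9).** p1 = 0.36, p2 = 0.51, m = 22 ASHAs per PHC, ICC = 0.02, two-sided 5%, 80% power.

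**Reproducing the stated 11.** Design effect = 1 + (22 − 1) × 0.02 = 1.42.
- Unpooled variance: (1.96 + 0.84)² × (0.36 × 0.64 + 0.51 × 0.49) / 0.15² gives 168 ASHAs per arm after rounding up. 168 × 1.42 / 22 = 10.84 PHCs (10.81 before rounding up to 168).
- Pooled variance: 171 ASHAs per arm. 171 × 1.42 / 22 = 11.04 PHCs.

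The stated 11 is therefore reproduced, but before any cluster is lost.

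**Power at the plan's own ICC.**
- All 11 per arm: effective n = 11 × 22 / 1.42 = 170.4. Power is 80.0% pooled, 80.7% unpooled.
- 10 per arm, after the stated loss: effective n = 10 × 22 / 1.42 = 154.9. Power is 76% pooled, 77% unpooled.

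The largest ICC that 11 per arm can carry at 80% power is 0.020 (pooled) to 0.021 (unpooled). At 10 per arm it is about 0.014 (pooled). The one variant that reaches 11 with the lost cluster included uses 25 ASHAs and the unpooled formula: 168 × 1.48 / 25 = 9.95, so 10 + 1 = 11. That ignores the loss of three ASHAs per PHC stated in the same sentence.

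**If the ICC is higher.** The ICCs below are illustrative assumptions; the documents give none but 0.02. The method is the plan's, with no cluster lost.

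| ICC | PHCs needed per arm | Power at 11 per arm |
|---|---|---|
| 0.03 | 13 | 74-75% |
| 0.05 | 16 | 64-65% |
| 0.10 | 24-25 | 47-48% |

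Ranges run over the pooled and unpooled formulas. Every row needs more PHCs than the frame holds.

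**How far the binary variance matters.** The formula treats each ASHA's MACCI as a yes/no result. Section 5.1 defines MACCI as a weighted average of nine proportions, so its SD is probably smaller. The documents give no SD. For an assumed SD s, power = Φ(0.15 / (s × √(2 / n_eff)) − 1.96). At ICC 0.10, n_eff = 11 × 22 / 3.1 = 78.1:
- s = 0.40: SE = 0.064, power 65%.
- s = 0.30: SE = 0.048, power 88%.

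At 11 per arm, 80% power holds for an SD up to about 0.41 at ICC 0.05 and about 0.33 at ICC 0.10.

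**The visit outcome.** For 0.46 versus 0.66, 11 PHCs per arm keep 80% power up to an ICC of about 0.077 (unpooled), so it is much less exposed.

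**The case against.** The strongest reply is that the revision clause is a planning statement made before randomisation and that the true position may be comfortable. Several parts of this stand.

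- A reader might infer that the only lever left is to move the target after seeing data. The sentence does not establish that: the definition of success can be read as an input to the revision. Any reset would also precede allocation, so it could not favour an arm, and no section makes the 15- or 20-point differences a success threshold for the test.
- The frame could be enlarged by amendment before randomisation. Section 7 describes Sagbara, which is not among the blocks in Section 6.3. The protocol does not plan this.
- Stratification on baseline MACCI is meant partly to improve power, and surveying more mothers per ASHA could sharpen each ASHA's index. The two-proportion formula credits neither.
- The binary variance is an upper bound for a composite, so the power table is not the true power of MACCI.
- It would be unfair to speak of undisclosed low power. Section 8 says openly that the ICC is assumed and that outcome data are lacking.
- With 23 eligible PHCs and 1:1 allocation, leaving one out is unavoidable. The defect there is only that Section 6.1 counts four PHCs as failing the criteria where Section 8 implies three.

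None of this gives the planned frame a twelfth PHC per arm, or makes the stated power include the cluster loss that it claims to include.

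**Conclusion.** The point stands in a limited form. Within the six blocks, the upward revision offered in Section 8 cannot be carried out, because the trial is capped at 11 PHCs per arm under either eligible count. On the plan's own method there is no margin: 80-81% power with all 11, and 76-77% with the one cluster per arm that Section 8 says may be lost. At assumed ICCs of 0.03 to 0.10, power falls to about 75% down to 48%.

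These figures rest on the plan's binary-variance formula and are conservative. The documents do not show that the trial is underpowered for MACCI; that depends on an SD and an ICC that only the baseline survey can supply. Nor do they show an intention to change the targets. What they show is a safeguard that the frame cannot honour, a power statement that does not include its own allowance for loss, an ambiguous clause on success, and two counts of eligible PHCs that disagree.

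**What to change.** In Section 8, replace the revision sentence with text to this effect: the number of PHCs is fixed at 11 per arm, the maximum within the six blocks at 1:1 allocation. Before randomisation, the baseline ICC, level and observed ASHA-level SD of MACCI will be used to recompute and report power, with and without loss of one PHC per arm, and the difference detectable at 80% power. The 15-point (MACCI) and 20-point (visits) targets will not be changed.

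In addition:
- Restate the present Section 8 power so that it reflects the stated loss of one cluster per arm and three ASHAs per PHC.
- Reconcile the 23 eligible PHCs in Section 8 with the 22 implied by Section 6.1. If 23 is correct, state how the 22 are chosen.

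The cost is protocol wording and a short recalculation once the baseline survey is done, with no extra data collection. The stated power may become slightly less favourable.

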**Table 9: Sample size calculation and associated assumptions**

|  |  | Ave value in control | Expected outcome in intervention | Ave number of individual per cluster | Number of cluster required |
| --- | --- | --- | --- | --- | --- |
|  | Proportion of neonates/mothers who received at least two postnatal home visits within first week of delivery by ASHA | **0.46** | **0.66** | **22** | **6** |
|  | MACCI (based on following assumptions) | **0.36** | **0.51** | **22** | **11** |
|  | Complete antenatal examination[[43]](#footnote-44) | **0.45** | **0.6** | **22** |  |
|  | At least 3 ASHA visits during pregnancyError: Reference source not found | **0.65** | **0.9** | **22** |  |
|  | Skilled birth attendanceError: Reference source not found | **0.85** | **0.90** | **22** |  |
|  | Neonates/mothers who received the recommended number of postnatal visitsError: Reference source not found | **0.05** | **0.30** | **22** |  |
|  | Exclusive breast feeding[[44]](#footnote-45) | **0.5** | **0.7** | **22** |  |
|  | DPT3 coverageError: Reference source not found | **0.67** | **0.67** | **22** |  |
|  | Sought care from ASHA for newborn complicationsError: Reference source not found | **0.27** | **0.5** | **10** |  |
|  | Sought care from ASHA for fever/ARIError: Reference source not found | **0.27** | **0.50** | **6** |  |
|  | Received ORS from ASHA for diarrhea within last two weeksError: Reference source not found | **0.65** | **0.75** | **6** |  |

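### The 11 PHCs per arm for MACCI allow for the three lost ASHAs per PHC but not for the lost PHC that Section 8 says is assumed; after that loss, power is about 76%, not 80%

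*Protocol*

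**What the plan says.** Section 8 takes the ASHA as the unit of analysis and the number of ASHAs in a PHC as the cluster size.

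- Starting values: "we assumed there will be 25 ASHAs in a PHC and MACCI of 36" percent.
- Clustering: "we will assume ICC to be 0.02", chosen because no data existed.
- Losses: "Assuming loss of one cluster per arm and three ASHAs per PHC, for detecting 15% absolute improvement in MACCI".
- Error rates: "compared to control arm at endline survey with 80% power and 5% two-sided significance level, we estimated that required sample size per arm will be". The figure given for MACCI is 11 PHCs.

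Table 9 gives the MACCI line as "MACCI (based on following assumptions) | 0.36 | 0.51 | 22 | 11": control value, intervention value, ASHAs per cluster, clusters required. Section 8 then randomizes eleven PHCs in each arm, and Section 6.1 agrees (22 in total). The same loss assumption is attached to the other primary outcome, two postnatal visits in the first week (46% versus 66%), for which six PHCs per arm are given.

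Section 8 also says that the size will be revised if the baseline survey differs greatly from the assumptions.

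**The concern.** A sample size that assumes the loss of one PHC per arm should randomize one PHC more than the analysis needs. Here the number required and the number randomized are both 11. Either the calculation needs only 10 PHCs at analysis, or the allowance was described but never added.

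In the second case, the stated power for a primary outcome fails under the very contingency that Section 8 says is covered. That contingency is realistic: Section 19 accepts that PHCs may drop out if the government reorganizes them. MACCI sets the size of the trial, so a null MACCI result after such a loss would be read as coming from a trial with 80% power when the plan's own formula gives less.

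**Working it through.** **Inputs.** Control 0.36, intervention 0.51, 22 ASHAs per PHC (Table 9); 25 ASHAs before loss, ICC 0.02, two-sided 5%, 80% power (Section 8). The normal quantiles are 1.960 and 0.842, and the square of their sum is 7.849. The protocol gives no SD for MACCI, so I treat it as a proportion with one yes/no observation per ASHA. This assumption reproduces the plan's figures.

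**Step 1: ASHAs per arm without clustering.**
- Unpooled variance: 7.849 × (0.36×0.64 + 0.51×0.49) / 0.15² = 7.849 × 0.4803 / 0.0225 = 167.5.
- Pooled variance under the null (mean proportion 0.435): [1.960×√(2×0.435×0.565) + 0.842×√0.4803]² / 0.0225 = 170.3.

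**Step 2: design effect.** 1 + (22 − 1) × 0.02 = 1.42.

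**Step 3: PHCs per arm needed at analysis.**
- Unpooled: 167.5 × 1.42 / 22 = 10.81.
- Pooled: 170.3 × 1.42 / 22 = 10.99.

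Both round up to the plan's 11. The 22 already carries the ASHA loss (25 − 3). No PHC has been added, and adding one gives 12.

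**Step 4: can 11 be 10 plus 1?** Other common variants at 22 ASHAs need more: 11.07 with the pooled variance in both terms, 11.84 with a continuity correction. At 25 ASHAs the design effect is 1 + 24 × 0.02 = 1.48, and the unpooled formula gives 167.5 × 1.48 / 25 = 9.92, so 10 + 1 = 11. That route drops the ASHA loss and contradicts the 22 in Table 9. None of these variants gives 11 with both losses included.

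**Step 5: the other outcome.** For 46% versus 66%, unpooled: 7.849 × (0.46×0.54 + 0.66×0.34) / 0.20² = 7.849 × 0.4728 / 0.04 = 92.8, and 92.8 × 1.42 / 22 = 5.99. This is the plan's six, again with no PHC to spare. Both Table 9 figures therefore come from the same route: 22 ASHAs per PHC and no PHC loss.

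**Step 6: power for MACCI.** The effective number per arm is PHCs × 22 / 1.42.

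| PHCs per arm at analysis | Effective n | Pooled | Unpooled |
| --- | --- | --- | --- |
| 11 | 170.4 | 80.0% | 80.7% |
| 10 | 154.9 | 76.2% | 76.9% |

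For 10 PHCs, unpooled: the standard error is √(0.4803/154.9) = 0.0557, the ratio is 0.15/0.0557 = 2.694, and Φ(2.694 − 1.960) = 76.9%. A t reference on 18 degrees of freedom lowers this to about 72%, but that reference is my choice; the protocol does not name one.

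**Step 7: detectable difference.** At 10 × 22 and a control value of 36%, 80% power needs 15.6 points (unpooled) or 15.7 points (pooled), so about 16 instead of 15.

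**Step 8: power for postnatal visits.** At 10 × 22, power is 94.7% (pooled) or 95.2% (unpooled).

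**The case against.** **The ASHA loss is included.** A reader might infer from Section 8 that neither loss entered the 11. Table 9 rules that out for the ASHAs, since 22 is 25 minus 3. Only the PHC loss is missing.

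**The 80% is not simply wrong.** A reader might conclude that the trial does not deliver 80% power for MACCI. With all 11 PHCs per arm retained, the plan's normal formula gives 80.0 to 80.7%. The shortfall arises only if the stated PHC loss occurs.

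**The variance may be too large.** MACCI averages nine coverage proportions, while the formula gives each ASHA the variance of one yes/no answer (SD 0.48 to 0.50). At 10 × 22, an SD of 0.47 would already restore 80% by the normal formula. This stands as a reason not to claim that true power is below 80%. It does not rescue the stated figure, because the documents give no SD and the 11 was evidently computed with the binary variance.

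**Lower figures can be produced.** Section 6.2 says "On an average, there are 20-25 ASHAs per PHC". Taking the low end of that range, or a t reference, brings power down further. Section 8 assumes 25, however, and Section 9.1 expects 250 to 300 ASHAs in the intervention area, or 23 to 27 per PHC over 11 PHCs. These are scenarios outside the plan's calculation, not errors in it.

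**The size is provisional.** Section 8 foresees a revision after baseline. Twelve per arm would need 24 PHCs, and Section 8 counts "total 26 PHCs, out of which 23 meet all eligibility criteria", so adding PHCs is not an option. A reader might infer that the revision must therefore fail. It need not: Section 8 also allows the definition of success to change, and a lower ICC would help. At an ICC of 0.01 the requirement is 167.5 × 1.21 / 22 = 9.2 PHCs, so 11 would cover a lost PHC.

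**Conclusion.** The point holds for the PHC loss alone. Section 8 attributes to the 11 PHCs an allowance that they do not contain. Under the plan's own inputs, 10.8 to 11.0 PHCs per arm must remain, so 12 would have to be randomized for the loss assumption to be true. After losing one PHC per arm, power for MACCI is about 76 to 77% by the plan's normal formula, a shortfall of 3 to 4 points, and the detectable difference is about 16 points.

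This rests on the ICC of 0.02, 22 ASHAs per PHC and the binary variance. Because the last of these is untested for an index, the finding is that the stated power does not follow from the stated assumptions, not that the trial is known to be underpowered. The postnatal-visit figure shares the omission without practical effect. The statement should be corrected because it concerns the stated power of a primary outcome and the correction is cheap.

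**What to change.** Keep 11 PHCs per arm. In Section 8, remove the claim that the 11 allow for a lost PHC, and say instead:

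- 11 PHCs per arm with 22 ASHAs each (25 less three lost) give 80% power for 36% versus 51% if no PHC is lost.
- After losing one PHC per arm, power is about 76% and the difference detectable with 80% power is about 16 points.
- Both figures treat MACCI as a binary proportion per ASHA with an ICC of 0.02.

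Correct the six PHCs for the postnatal-visit outcome in the same way: six is the number needed at analysis and seven with a lost PHC. Note that the 11 randomized keep about 95% power for that outcome after the loss. Label the Table 9 column as PHCs needed at analysis.

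When the size is revisited after baseline, recompute MACCI with a formula for two means, using the baseline ASHA-level SD and ICC.

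The cost is a few sentences and a slightly less favourable power statement. No PHCs are added, and randomization, conduct and analysis do not change.

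### On Section 8's own inputs, 11 and six PHCs per arm reach 80% power only with normal quantiles and no lost cluster; t quantiles and the stated loss of one cluster give about 72% and 61%

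*Protocol*

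**What the plan says.** Section 8 assumes 25 ASHAs per PHC, a loss of three ASHAs per PHC and of one cluster per arm, and, for the ICC, "we will assume ICC to be 0.02". It sizes the trial "for detecting 15% absolute improvement in MACCI in intervention arm compared to control arm" and concludes "with 80% power and 5% two-sided significance level, we estimated that required sample size per arm will be 11 PHCs/clusters". For the proportion with at least two postnatal visits in the first week, it says "we estimated that required sample size per arm will be six PHCs/clusters for detecting 20% absolute improvement", at the same power and level.

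Table 9 carries the inputs: for MACCI, control value, intervention value, individuals per cluster and clusters read "0.36 | 0.51 | 22 | 11". The other outcome has 0.46, 0.66, 22 and 6. The 22 is the 25 ASHAs less the three assumed lost.

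Eleven PHCs per arm are randomized for both outcomes. No formula, type of quantile or variation in PHC size is given; Section 6.2 says only "On an average, there are 20-25 ASHAs per PHC". Section 15.4 accounts for clustering, uses GEE for adjustment and refers to the SAP.

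**The concern.** Two features of the calculation look optimistic. With 11 PHCs per arm, a between-cluster comparison has about 20 degrees of freedom, so its two-sided 5% critical value is 2.09, not 1.96. With six per arm there are 10, and the value is 2.23. Section 8 also says that its numbers allow for one lost cluster per arm, yet they equal what the formula gives with none lost.

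The stake is the power claim for MACCI, the outcome that sets the trial's size. Section 8 foresees revising the sample size after the baseline survey if the assumptions prove far off, and that revision should not repeat the same calculation.

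**Working it through.** **Inputs (Section 8, Table 9).** MACCI 0.36 vs 0.51; postnatal visits 0.46 vs 0.66; m = 22 ASHAs per PHC; ICC 0.02; two-sided 5%; 80% power. Design effect = 1 + (22 − 1) × 0.02 = 1.42.

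**Reproducing the stated numbers.** n per arm = (1.96 + 0.84)² × (p₁q₁ + p₂q₂) / d², and PHCs per arm = n × 1.42 / 22.

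- MACCI: p₁q₁ + p₂q₂ = 0.2304 + 0.2499 = 0.4803; n = 167.5; 167.5 × 1.42 / 22 = 10.81, so 11.
- Postnatal visits: 0.2484 + 0.2244 = 0.4728; n = 92.8; 92.8 × 1.42 / 22 = 5.99, so 6.

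A pooled variance gives 11.04 and 6.20 instead. The unpooled form matches both stated integers. Adding the one lost cluster gives 11.81 and 6.99, that is 12 and 7, even with normal quantiles.

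**Power.** SE = √[(p₁q₁ + p₂q₂) × 1.42 / (k × 22)]. Normal power is Φ(d/SE − 1.96). The t-based power uses the non-central t on 2k − 2 df with non-centrality d/SE. For MACCI at k = 11, SE = 0.0531 and d/SE = 2.83.

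| Outcome | PHCs per arm analysed | df | Normal | t |
|---|---|---|---|---|
| MACCI | 11 (none lost) | 20 | 80.7% | 76.7% |
| MACCI | 10 (one lost) | 18 | 76.9% | 72.2% |
| MACCI | 12 | 22 | 83.9% | 80.5% |
| Postnatal visits | 6 (none lost) | 10 | 80.1% | 71.5% |
| Postnatal visits | 5 (one lost) | 8 | 72.6% | 61.3% |
| Postnatal visits | 7 | 12 | 85.7% | 79.4% |
| Postnatal visits | 8 | 14 | 89.9% | 85.3% |
| Postnatal visits | 10 | 18 | 95.2% | 92.8% |
| Postnatal visits | 11 | 20 | 96.7% | 95.0% |

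With t quantiles, seven PHCs fall just short for the postnatal-visit outcome, so eight are needed, or nine with one lost.

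**Unequal PHC size.** With design effect 1 + [(1 + CV²) × 22 − 1] × 0.02 and an assumed CV of 0.2 to 0.4, MACCI power at 11 PHCs falls from 76.7% to between 76.2% and 74.7%. The Protocol gives no CV.

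**Variance of MACCI.** The calculation above treats MACCI as yes/no, with SD √0.2304 = 0.48 and √0.2499 = 0.50. MACCI is a weighted average of nine coverages, each between 0 and 1. Its SD cannot exceed the weighted average of the component SDs, and each of those is at most √(pq). Table 9's component rates give these domain averages:

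- Control: maternal 0.444, newborn 0.218, infant 0.485, morbidity 0.455; mean 0.40.
- Intervention: 0.363, 0.458, 0.464, 0.478; mean 0.44.

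With those caps and the same t test, power for 15 points is at least 87.8% with 11 PHCs and 84.2% with 10. One caution: with equal domain weights, the same component rates average 0.42 and 0.59, not the stated 0.36 and 0.51, so the caps rest on rates that do not reproduce the stated index.

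**The case against.** The strongest objection is that 77% or 72% is not the real power for MACCI. The bound from Table 9's component rates puts the SD well below the yes/no value and power above 80%, even with t quantiles and one PHC lost. This stands. A reader might infer that the trial is underpowered for MACCI; the documents do not support that. They support only that the stated 80% does not follow from the basis Section 8 appears to use.

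Second, 22 ASHAs is already a post-loss count. With 25 ASHAs and 11 PHCs, nothing lost, t quantiles give 80.1%. So the shortfall cannot be said to hold with full retention. For MACCI, 11 can also be reached from 25 ASHAs plus one lost cluster (9.92 + 1 = 10.92). That route omits the ASHA loss that Section 8 and Table 9 both apply, and gives 6.49, not 6, for the other outcome.

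Third, the six has no practical effect, because 11 PHCs per arm are randomized. This stands too.

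Fourth, unequal PHC size might be read as a cause of the 77% and 72%. It is not: both come from equal sizes and the t reference alone, and any further loss rests on an assumed CV.

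Fifth, the quantiles are inferred, and the unseen SAP may specify a small-sample correction. An inflated type I error therefore cannot be asserted. Such a correction would not restore the stated 80%, however; it would bring in the t reference used here.

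Finally, the ICC is a declared guess. With t quantiles, 0.01 gives 83% and 0.03 gives 71% for MACCI at 11 PHCs, a wider range than the four-point quantile effect.

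**Conclusion.** The point holds as a misstatement in Section 8. On yes/no variance, 22 ASHAs per PHC, ICC 0.02 and two-sided 5%, 11 and six PHCs per arm reach 80% only with normal quantiles and every cluster retained. The t reference alone lowers power to about 77% and 72%. With the cluster loss that Section 8 itself assumes, it is about 72% and 61%, or 77% and 73% with normal quantiles. The uncounted cluster is the firmer of the two errors, since it needs no view on the test to be used.

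The consequence is limited. The postnatal-visit outcome has 93–95% power at the size randomized. Actual MACCI power depends on an ASHA-level SD that the Protocol does not give, and may exceed 80%.

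**What to change.** Recompute Section 8 with t quantiles on the between-PHC degrees of freedom and with the stated loss of one cluster per arm counted.

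- **MACCI:** either restate power for 11 randomized PHCs per arm as about 72% on the yes/no variance (77% if no PHC is lost), or use an ASHA-level SD for the composite score, for example from the baseline survey, and report the power that results.
- **Postnatal visits:** change six to eight PHCs per arm (nine with one lost), and note that the 11 randomized give about 93–95%.
- **PHC size:** base any allowance for unequal size on the observed ASHA counts, not an assumed CV.

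Do not add clusters. The case for more is not made, and 12 per arm would need 24 PHCs where Section 8 counts 23 eligible. The cost is restated figures in Section 8 and Table 9 and, if the yes/no variance is kept, a lower stated power for MACCI.
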